## Trial design {8}

UPlusE is a prospective, cluster-randomized controlled trial conducted in an outpatient setting. The intervention (screening and, if indicated, consultation by treating doctors) is a new form of healthcare provision. In line with this, UPlusE is being implemented and evaluated within the normal healthcare context. UPlusE is an experimental study within a superiority framework. The effects of the UPlusE intervention will be evaluated by comparing the intervention group with the control group, which receives treatment as usual. If the intervention works as intended, the intervention group will have better values for primary and secondary outcomes. The practices are randomized into an intervention and a control group (1:1 ratio, ensuring an equal distribution of 50% to both groups). The cluster randomization is chosen because the intervention will affect the organizational structure of the entire practice: this includes participant-specific, organizational, and implementation aspects. Thus, counselling parents with mental health/psychosocial issues and encouraging them to utilize the services of mental health practitioners or support services is a responsibility of the entire practice. The cluster randomization ensures that participants in each practice either receive the intervention or serve as the control group, depending on the practice’s assignment. Participants will be recruited nationally from participating paediatric and gynaecological practices. Through screening for depression and psychosocial stress, both groups are expected to yield positive (screened positive) and negative (screened negative) results. In the intervention group, participants receive the intervention as soon as a positive result occurs. Participants in the control group receive treatment as usual. For assessing the success of the intervention (clinical evaluation), comparing participants from both groups with positive results is relevant. Participants in the control group with negative results will additionally be observed concerning the natural course of events from the inclusion point up to U6. The study design is depicted in Fig. 1.

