### Sample size {14}

The proportion of all parents who avail themselves of any mental health services is based on the available figures. (18% [22], health insurance data: 10–12%) and is assumed to be 15% in the following. The assumption is that through the intervention, the proportion of affected parents using mental health services can be increased to at least 25% in the intervention group. With *α* < 0.05 and a power of 0.80, a sample size of 500 subjects is therefore required. The cluster-randomized controlled design must be considered when calculating the required number of participants. The design effect due to cluster randomization is estimated at 1.725 (intra-cluster correlation (ICC): 0.15; number of patients/practices: 2.5). With a dropout rate of 20%, the number of required positively screened subjects is (500 × 1.725) / 0.80 = 1078. Given a known prevalence of peripartum depression of 10–15% as the condition that is in our focus, a total of 10,000 parents (5000 each in the intervention and control groups) must be screened and included (Fig. 3).

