## Statistical methods

### Statistical methods for primary and secondary outcomes {20a}

The intervention in UPlusE will be scientifically evaluated using a multidimensional approach and various methods (multilevel analyses, process analyses, secondary data analysis) that, in combination, allow for a comprehensive assessment of different aspects of the project.

All data analyses will be conducted using pseudonymized data. After the observation period (U6), the primary and secondary endpoints for parents with psychological and psychosocial issues will be analysed in a group comparison (comparison between the intervention and the control group). Multilevel analyses will be conducted based on the intention-to-treat principle.

Additionally, the trajectory of values and the utilization of services for parents without psychological and psychosocial issues at the time of project inclusion (clinical evaluation) will be descriptively analysed. Quantitative parameters will be analysed using multilevel analyses to correct for cluster randomization. In the case of structural inequality between the intervention and control groups, relevant parameters (such as age, gender, number of pregnancies and births, partnership, socioeconomics—education, occupation, financial situation, severity of depression) will be adjusted for. All tests will be two-tailed with a significance level of alpha = 0.05.

In the analysis, a descriptive evaluation (e.g. symptom severity, child symptoms, service utilization) will be conducted for the group of parents who were positively screened. At the time of U6, a comparison between the intervention and control groups will be performed (e.g. symptom severity, parent–child bonding, child symptoms). Furthermore, across groups, psychosocial stress, depressive symptoms, stigma, and service utilization will be assessed.

The data from the process analysis questionnaires will be analysed descriptively and inferentially.

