In a regional pilot project in Nuremberg, over the course of 21 months (from April 2020 to December 2021) during the SARS-CoV-2-pandemic and without additional compensation, *N* = 5235 women were screened in gynaecology and paediatric practices using the EPDS [25]. The acceptance among both gynaecologists and paediatricians was very high, feasibility found to be good. The EPDS also included questions about traumatic birth and experiences of violence. Overall, a prevalence of pregnancy depression (defined using an EPDS cutoff ≥ 10) was found to be 9.94%, with 43.9% of women having an EPDS total score > 12. The prevalence of postpartum depression was 10.18%, with 46.9% having an EPDS total score > 12; 10.87% of women reported experiences of violence, while 19.64% of postpartum surveyed women reported a traumatically experienced birth; in contrast, 4.53% indicated both experiences of violence and a traumatically experienced birth. The following statements about the pilot project were documented by the participating paediatric and gynaecology practices: ‘I was surprised by the percentage of mothers showing symptoms – thinking back to the time before screening in terms of undetected mothers,’ ‘The patients are very satisfied with the screening – they appreciate being asked about their mental well-being,’ ‘What's remarkable is that a significant number of affected mothers only discuss it openly after the questionnaire is addressed due to conspicuous responses,’ ‘The plus-questions help identify pregnant women who require special trauma-sensitive care during childbirth’. Mothers found it indeed helpful to be addressed about a conspicuous result in the questionnaire. Overall, the dropout rate was very low (1.22%). In a survey conducted by Schatten & Licht e.V. (self-help organization for peripartum mental disorders), 97% of the affected individuals (*N* = 58) endorsed the screening as described above. As a conclusion for UPlusE, a high acceptance among healthcare providers and patients can be inferred [25, 29].

With utilization as the primary outcome, UPlusE will provide evidence that more mothers/parents with depression and/or psychosocial burdens seek treatment or counselling. We also expect to provide evidence for an improvement of mental health in young families, an increase of unimpaired parent–child relationships, a decrease of psychosocial burdens, and an improvement of regulatory problems in children.

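### The design effect of 1.725 does not follow from the stated ICC of 0.15 and 2.5 patients per practice, which give 1.225; the 1078 positives and the 80% power do not match the plan's own inputs

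*Protocol article*

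**What the plan says.** All the figures stand in the protocol article, mostly under Sample size {14}.

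- The control proportion using services "is assumed to be 15% in the following", and the assumption is that "the proportion of affected parents using mental health services can be increased to at least 25% in the intervention group".
- With alpha 0.05 "and a power of 0.80, a sample size of 500 subjects is therefore required". Statistical methods {20a} adds: "All tests will be two-tailed with a significance level of alpha = 0.05".
- Allocation is by practice. Trial design {8}: "The practices are randomized into an intervention and a control group (1:1 ratio, ensuring an equal distribution of 50% to both groups".
- The clustering step reads: "The design effect due to cluster randomization is estimated at 1.725 (intra-cluster correlation (ICC): 0.15; number of patients/practices: 2.5".
- After 20% dropout, "the number of required positively screened subjects is" given as (500 × 1.725)/0.80 = 1078. From a prevalence of 10–15% the article then arrives at 10,000 parents to be screened, 5000 per group.

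**The concern.** The design effect and its two inputs stand in the same sentence and do not agree. The figure is not a misprint confined to one place: 1.725 is used again in the next step and produces 1078, which in turn leads to the 10,000. The article shows the whole calculation, so this is a wrong statement and not a detail left to a fuller document.

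At stake is whether the stated power can be defended. If the inputs are right, the trial is larger than 80% power requires. If the design effect is right, at least one input is wrong or unstated, and the size is about what is needed. The two cases call for different decisions about the target, and the article does not let the reader tell them apart.

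**Working it through.** **Inputs.** 15% and 25%; power 0.80; ICC 0.15; m = 2.5 patients per practice; dropout 20%; prevalence 10–15% (all Sample size {14}). Two-sided alpha 0.05 ({20a}). Allocation 1:1 ({8}).

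**Step 1: unadjusted size.** Two proportions, normal approximation, pooled variance under the null:

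n per arm = [1.96 × √(2 × 0.20 × 0.80) + 0.842 × √(0.15 × 0.85 + 0.25 × 0.75)]² / 0.10² = 249.98, so 250 per arm and 500 in total. The plan's 500 reproduces.

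**Step 2: the plan's inflation.** 500 × 1.725 = 862.5, and 862.5/0.80 = 1078.1. The plan's 1078 reproduces if 1.725 is taken as given.

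**Step 3: the design effect from its stated inputs.** DE = 1 + (m − 1) × ICC = 1 + 1.5 × 0.15 = **1.225**. The variant 1 + m × ICC gives 1.375, so it does not explain 1.725 either. If the 2.5 counts patients before dropout, the analysed cluster size is 2.5 × 0.80 = 2.0 and the design effect is 1 + 1.0 × 0.15 = 1.15, further still from 1.725.

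**Step 4: what would give 1.725.**

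- A larger cluster: m = 1 + 0.725/0.15 = 5.83.
- A larger ICC: 0.725/1.5 = 0.483.
- Unequal clusters, DE = 1 + [(CV² + 1) × m − 1] × ICC: CV² = 5.83/2.5 − 1 = 1.33, so CV is about 1.15.
- Misplaced terms: (2.5 − 1) × (1 + 0.15) = 1.725 exactly.

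The first three are not stated anywhere. The fourth is an inference from the exact match; the article prints no formula.

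**Step 5: consequences if the stated inputs are right (DE 1.225).**

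- Required positives: 500 × 1.225/0.80 = 765.6, so 766. The stated 1078 is 1078/766 = 1.41 times that, about 41% more.
- Number to screen: 765.6/0.10 = 7,656 at 10% prevalence; 765.6/0.15 = 5,104 at 15%.
- Power at 1078 positives: effective size 1078 × 0.80/1.225 = 704, or 352 per arm; z = (0.10 × √352 − 1.109)/0.561 = 1.37, so power is about 91%.

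**Step 6: consequences if 1.725 is right.**

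- 1078 positives give 80% power, as stated.
- 766 positives give an effective size of 766 × 0.80/1.725 = 355, about 178 per arm, and power of about 66%.

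**The case against.** The strongest counter-argument is that the error is harmless. On the plan's own inputs it is conservative: more positives are sought than 80% power requires. The exact match with (2.5 − 1) × (1 + 0.15) also makes a slip in the formula more plausible than a hidden larger cluster or ICC. This stands as far as it goes. It shows that the trial is not demonstrably too small, but it does not make the stated design effect, required number or power correct.

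Three stronger readings are tempting, and the documents do not support them.

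- *The 10,000 falls short of 1078 positives.* A reader might set the pilot figures (9.94% in pregnancy; in the Discussion, "The prevalence of postpartum depression was 10.18" per cent) against the 1078/10,000 = 10.78% needed. But at the stated 10–15% the number to screen runs from 1078/0.15 = 7,187 to 1078/0.10 = 10,780, and 10,000 lies inside that range. The pilot rates also count only women with EPDS of 10 or more, whereas a positive screen here includes KID-PROTEKT and PBQ scale 1, and Intervention description {11a} lets initially negative parents turn positive later.
- *Too few practices will leave the trial underpowered.* The article gives no number of practices, so any low figure would be the reader's own assumption. A practice target and its monitoring are details that a condensed article may leave to the full protocol.
- *Recruitment ends on the participant count alone.* Trial status also gives a calendar end, 30 April 2026.

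**Conclusion.** The point holds in a narrow form. The design effect of 1.725 is wrong for an ICC of 0.15 and 2.5 patients per practice; the correct value is 1.225. Taken at face value, those inputs require 766 positives instead of 1078, and 1078 would give about 91% power instead of 80%. The 10,000 fails to match the inputs only through the design effect; the conversion by prevalence is not a separate error.

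These figures assume the usual design effect with equal cluster sizes, the normal approximation that reproduces the plan's 500, and dropout of individuals at 20%. Which element is wrong (the design effect, the ICC, the cluster size, or an unstated allowance for unequal clusters) cannot be settled from the article. A conclusion that the trial is underpowered would need inputs that it does not state.

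**What to change.** In Sample size {14}, first establish which inputs were intended: the ICC, the mean number of positively screened parents per practice (before or after dropout) and, if one was used, the coefficient of variation of cluster size. State the formula. Then restate together the design effect, the required number of positives, the number to screen across the 10–15% prevalence range, and the power.

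If ICC 0.15 and 2.5 per practice are confirmed, give 1.225 and 766, and report about 91% power should the target of 1078 positives be kept. If 1.725 is confirmed, give the inputs that produce it. Keep the present target until this is done, because reducing it to 766 under a true design effect of 1.725 would cost about 14 percentage points of power (80% to 66%).

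The cost is a correction to the protocol wording, and to the registration if it carries the same figures. No extra enrolment is needed.

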### Recruitment {15}

With the current usage of the ‘My Paediatric Practice’ app by 750,000 parents and a daily increase of approximately 1000 parents, we consider achieving the required sample size as very realistic. UPlusE is a module of the BKK health care program ‘Strong Kids’ but will still be open to insured individuals from other insurers.

## Assignment of interventions: allocation

### Sequence generation {16a}

Following the confirmation of physicians’ participation in UPlusE, practices are randomly assigned to either the intervention or the control group (cluster randomization). The confirmation and randomization processes take place automatically within the practice app administration (opt-out regulation), with separate procedures for gynaecologists and paediatricians. The allocation to the groups is maintained at a 1:1 ratio, ensuring an equal distribution of 50% of physicians to both the intervention and control groups. To achieve this, randomization lists are generated in advance by the evaluation team using statistical software SAS 9.4 (TS Level 1M7 Copyright © 2016 by SAS Institute Inc., Cary, NC, USA) employing the method of simple random sampling (proc surveyselect). Participating practices are included in these randomization lists. To maintain a balanced ratio of intervention to control practices within regions, the inclusion in the list is organized by postal code. The automated nature of the randomization process precludes any external influence on its outcome.

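### Simple random sampling on lists drawn up in advance does not by itself secure the claimed balance of practices within regions, and an exact 50% split holds only if the lists are fully used

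*Protocol article*

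**What the plan says.** Everything is in the protocol article under Sequence generation {16a}.

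- **Unit:** once physicians have confirmed that they take part, "practices are randomly assigned to either the intervention or the control group (cluster randomization").
- **Ratio:** "The allocation to the groups is maintained at a 1:1 ratio, ensuring an equal distribution of 50% of physicians" to each arm. The Trial design section {8} makes the same claim.
- **Lists:** "randomization lists are generated in advance by the evaluation team", "employing the method of simple random sampling (proc surveyselect").
- **Filling:** "Participating practices are included in these randomization lists".
- **Region:** "To maintain a balanced ratio of intervention to control practices within regions, the inclusion in the list is organized by postal code".
- **Specialty:** the process runs "with separate procedures for gynaecologists and paediatricians".

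The section names no blocks, regional strata, minimisation or list length. It does not say whether the postal-code device is a sort order or a set of separate lists.

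Under Statistical methods {20a}, covariates enter only if the arms turn out structurally unequal. The examples given there are parent characteristics and depression severity; region and specialty are not among them.

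**The concern.** The section names a method and claims a property that the method does not supply. Simple random sampling of a list constrains one number, the count selected from that list. It puts no constraint on any subset, such as the practices of one region.

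Region plausibly matters for the primary outcome, which is use of mental health and early prevention services. The intervention works partly by handing out regional addresses (Intervention description {11a}), and waiting time for support is one of the study questions (Objectives {7}). If the arms differ by chance in local service supply, the utilization comparison carries that difference. The planned adjustment does not clearly remove it, because region is not named and adjustment depends on finding inequality first.

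**Working it through.** **Inputs from the article.** 1:1 ratio; simple random sampling; lists made in advance ({16a}). 1078 positively screened subjects and 2.5 patients per practice (Sample size {14}).

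**Assumptions.** The article gives no number of practices, region size or list length. 1078 / 2.5 = 431.2, so about 431 practices; 432 is used as an even list length. Region sizes (4, 10, 20) and regional list lengths (20, 40, 100) are illustrative. The two specialties are pooled in one list for simplicity.

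**The stated 50% split.** Let a list have L slots, of which L/2 are drawn at random for intervention, and let r practices take slots. The number X in the intervention arm is hypergeometric:

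P(X = k) = C(L/2, k) · C(L/2, r − k) / C(L, r)

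- L = 432, r = 432: X = 216 with certainty. The 50% claim is reproduced when the list is fully used.
- L = 600, r = 432: P(216:216) = 0.07; 95% range 205 to 227.
- L = 1000, r = 432: P(216:216) = 0.05; 95% range 201 to 231.

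The cost of an unequal split s : (1 − s) is small. Relative information is 4s(1 − s), which at s = 0.55 is 4 × 0.55 × 0.45 = 0.99.

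**Balance within a region, one list sorted by postal code.** Under simple random sampling every subset of r slots has the same distribution, wherever it sits in the list. Sorting therefore changes no probability. With L = 432 fully used:

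| Practices in region | Event | Probability |
|---|---|---|
| 4 | all in one arm | 0.12 |
| 10 | exactly 5:5 | 0.25 |
| 10 | 7:3 or worse | 0.34 |
| 20 | 14:6 or worse | 0.11 |

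Independent 50:50 draws give almost the same for 10 practices: 2 × (1 + 10 + 45 + 120) / 1024 = 352 / 1024 = 0.344.

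**Balance within a region, separate list per region, r = 10.**

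| Slots on regional list | P(5:5) | P(7:3 or worse) |
|---|---|---|
| 10 (fully used) | 1.00 | 0 |
| 20 | 0.34 | 0.18 |
| 40 | 0.28 | 0.27 |
| 100 | 0.26 | 0.32 |

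**Benchmark with permuted blocks within region and specialty.** Take 10 practices in a region, divided between two specialties. With blocks of 4, the specialty counts leave remainders after full blocks of 0 and 2, 1 and 1, or 3 and 3. The arms then differ by at most 2 in total, so the worst split is 6:4. With blocks of 2 the split is 5:5 if both specialty counts are even and at worst 6:4 if both are odd.

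**The case against.** **The 50% split may be exact.** Drawing half of a list without replacement gives exactly 50% once the list is used up. This stands: a reader might infer that the 50% claim is false, and the article does not support that. It is only not ensured unless the lists are fully used.

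**Separate postal-code lists may have been used.** Half drawn from each of several completely filled regional lists is stratified randomisation and balances exactly. The article mentions an opt-out rule and says that practices are placed on the lists, which can be read as lists of known practices. This also stands as a possibility, so it would be wrong to say that separating lists cannot work. The text equally allows empty slots filled as practices confirm, and then the balance is lost.

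**An article condenses the full protocol.** The SAS procedure can combine simple random sampling with strata, and block sizes are often left to the full document. That excuses missing detail. It does not settle a claim of regional balance that rests on a method which, as named, lacks a balancing device.

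**The consequence is limited.** Allocation is random and unbiased, and regional imbalances in different directions tend to offset. Specialty is already handled separately. Baseline equivalence is to be checked {21b}, the covariate list in {20a} is not exhaustive, and inverse probability weighting is held in reserve {20c}. All of this stands and keeps the point modest. However, none of these provisions names region, and each responds only to observed inequality.

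**Conclusion.** The concern holds in a limited form. The method described in {16a} does not by itself ensure balance between arms within regions. Sorting by postal code has no effect on that balance, and separate regional lists secure it only if each is completely used. The same condition applies to the overall 50% split.

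For an assumed region of 10 practices, a split of 7:3 or worse has probability about 0.34 from one long list and 0.18 to 0.32 from regional lists of 20 to 100 slots. These figures illustrate the mechanism; they do not measure this trial, because the article gives no region or list sizes.

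A reader might infer biased allocation or a material loss of power. The documents support neither: assignment is random, and even a 55:45 split keeps 99% of the information. What remains is a chance regional imbalance in service supply. Its effect on utilization is plausible but not quantified in the article, and the planned adjustment does not name region. The point should be corrected but does not threaten the trial.

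**What to change.** 1. **Analysis.** Prespecify coarse postal-code region and specialty as covariates in the primary multilevel model, whatever imbalance is observed. This remains possible before the analysis even if all practices are assigned. It costs a few extra model parameters.
2. **Practices not yet assigned.** Use permuted blocks within coarse region inside each specialty's existing procedure, and state the regions and the rule for filling lists. Participant recruitment began on 9 February 2024, so this is a list update during the trial that must be notified as a protocol change (section {25}). Some blocks will stay incomplete, and for that reason regions should be coarse.
3. **If assignment is complete** and neither blocking nor fully used regional lists were in place, replace the claims of regional balance and of an ensured 50% split with the actual counts by arm, region and specialty. If such a device was in place, describe it in {16a}. Either way the cost is a sentence or a small table.
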